**Figure 1 F1:**
[figure not shown]
Characteristics of the study group and interventions’ description.

All participants will be given drugs (IMP or placebo) by nebulization with the use of the same device—AEROGEN SOLO® (Aerogen Ltd, Galway, Ireland). This is an innovative tool which delivers aerosol *via* a vibrating mesh. Evidence suggests that the vibrating mesh nebulizer (VMN) provides a 5-fold greater aerosol delivery to the lung as compared to a jet nebulizer (JN). The nebulizer will be placed in the respiratory circuit at a short distance from the CPAP interface.

Echocardiography will be conducted at least twice during the study: (1) within 6 h after enrolment in the study and (2) 6–10 h after administration of the last dose of the drug (or placebo).

LUS will also be conducted twice during the study: (1) within 6 h after enrolment in the study, ideally simultaneously with the CXR and (2) 6–10 h after administration of the last dose of the drug (or placebo).

The modified TTN Silverman score will be determined every 1 h during the first 6 h after enrolment, every 2 h between 6 and 24 h after enrolment, and every 6 h from 24 to 48 h after enrolment.

The modified TTN Silverman score will be determined at 1 and 4 h after administration of the drug (or placebo) and at the moment of intubation (if needed). Vital signs, including respiratory rate, heart rate, fraction of inspired oxygen (FiO_2_), blood pressure (systolic, diastolic, and mean) and arterial blood oxygen saturation, will be recorded every 1 h during the first 24 h after enrolment and every 2 h between 24 and 48 h after enrolment. Additionally, vital signs will be evaluated 1 and 4 h after administration of the drug (or placebo).

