#### Inclusion criteria

2.3.4.

The inclusion criteria are as follows:
a.Gestational age at birth between 32 and 42 weeks.b.Respiratory disorders (tachypnea and expiratory grunting) lasting longer than 15 min after birth, present for at least 15 min in the first 6 h of life, or a need for noninvasive respiratory support between birth and 6 h of life.c.Available chest radiography obtained within 6 h after birth.d.Available parameters of the acid–base balance (blood pH, partial pressure of O_2_ and CO_2_, and base excess) and blood serum ionogram for Na^+^, K^+^, and Ca^2+^ evaluated in the umbilical cord blood sample.

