#### Exclusion criteria

2.3.5.

The exclusion criteria are as follows:
a.Need for intubation directly after birth or perinatal asphyxia, defined as the abnormal acid–base parameters detected in an umbilical cord blood sample (pH < 7.0 or base excess ≤14 mmol/L).b.Multiple apnea-brady that require immediate intubation prior to an NIV trialc.Age > 24 h.d.Meconium aspiration syndrome.e.Air leak syndrome.f.Congenital heart disease.g.Congenital diaphragmatic hernia.h.Other severe congenital malformations and genetic disorders (diagnosed before and after birth) associated with an increased risk of respiratory failure.i.The need for surfactant administration immediately after birth, regardless of the method of administration (respiratory distress syndrome—RDS).

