### Procedures and interventions

2.4.

Enrolment will take place within and up to 24 h from birth (usually within the first 6 h of life). During enrolment, patients will be screened for the inclusion and exclusion criteria. Demographic data (including date and time of birth, sex, gestational age in weeks and days, and body weight at birth), obstetric history [type of delivery, single/multiple pregnancy, and prenatal steroid treatment (number of doses and date of last dose administered)], and Apgar scores will be collected, and physical examination will be conducted.

Researchers can use a variety of CPAP or NIV devices or modes, e.g., DuoPAP on FABIAN® (ACUTRONIC Medical Systems AG, Switzerland), CMV on Babylog® VN500 (Drägerwerk AG Co., Germany). Based on the available literature, it is not possible to clearly demonstrate the advantage of one of the modes of respiratory support over another in the treatment of respiratory failure in newborns. We would like the study to determine whether this is indeed the case and to what extent the change in the mode of non-invasive ventilation impacts the incidence of PPHN. Proposed CPAP initial settings: PEEP at 5–6 cm H_2_O pressure with an oxygen concentration of ≥21% to maintain pre-ductal saturation between 90% and 95%.

Patients assigned to the study group will be treated with 0.15 mg/kg body weight (diluted in 3 ml 0.9% NaCl) nebulized salbutamol (Ventolin®, GlaxoSmithKline, Dublin, Ireland) for 30 min. This dose was selected according to a previous study on salbutamol in TTN (31). The placebo group will be administered 3 ml nebulized 0.9% NaCl for 30 min.

The intervention period (during which patients will receive salbutamol or 0.9% NaCl together with NIV) will be divided into period I up to 24 h after enrolment and period II between 24 and 48 h after enrolment. Patients can be treated for up to 48 h from enrolment, with a maximum of four doses administered every 6 h. The extended follow-up period is planned between 48 h after enrolment and 7 days of life (or hospital discharge, whichever occurs first). The study design and planned examinations are shown in Figure 1.

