### Primary outcome

2.6.

The primary outcome is the percentage of infants who develop PPHN, defined as the need for ventilation with FiO_2_ > 0.30 and features of increased pulmonary pressure on echocardiogram (patent ductus arteriosus or foramen ovale with right-to-left or bidirectional flow, as well as other echocardiographic parameters described below), and/or a > 10% difference between pre-ductal and post-ductal oxygen saturation levels.

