**Figure 2 F2:**
[figure not shown]
The schedule of enrolment, interventions, and assessments in the REFSAL study. D – possible performance of an additional examination according to the decision of the attending physician. Obligatory in the case of intubation, pneumothorax, or sudden deterioration of the patient's condition – procedures should be performed within 6–10 h of the patient's deterioration. ^a^Blood count, Ionogram made of venous blood, Blood gases. ^b^Every 1 h within 6 hours of randomization, every 2 h between 6 and 24 h, and every 6 h between 24 and 48 h after randomization and 1 and 4 h after the end of each dose/placebo and at the time when intubation is necessary. ^c^Every 1 h within 6 h of randomization, every 2 hours between 6 and 24 h, every 6 h between 24 and 48 h after randomization, and 1 and 4 h after the end of each dose/placebo and at the time of necessity for intubation. * Adverse events monitored from enrolment until the end of the extended follow-up period, that is, up to seven days of age or hospital discharge. **up to 6 hours after allocation. ^+^6–10 hours after the last dose of IMP.

The examination will include the following:

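### PPHN present at entry is neither excluded nor reliably measured before treatment, so existing cases may be mixed with new ones in a prevention outcome

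*Protocol article*

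**What the plan says.** **Aim and outcome.** The hypothesis (section 2.1) is about preventing PPHN from developing. Section 2.6 states: "The primary outcome is the percentage of infants who develop PPHN". The definition there, repeated in section 2.8, combines a need for ventilation above an FiO2 threshold, echocardiographic signs and a gap between pre- and post-ductal saturation. Neither section says from when the outcome is counted, or what happens to an infant who meets the definition on the first examination. Section 2.3.3 compares incidence between the arms and states no restriction to infants free of PPHN at entry.

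**Entry.** Section 2.3.4 requires a radiograph ("Available chest radiography obtained within 6 h after birth") and cord-blood tests, but no echocardiogram. Section 2.3.5 has nine exclusions, a to i. The cardiopulmonary ones include "Meconium aspiration syndrome.e.Air leak syndrome.f.Congenital heart disease.g.Congenital diaphragmatic hernia". None names PPHN, raised pulmonary pressure, right-to-left shunting or a saturation gap. On timing, section 2.4 says: "Enrolment will take place within and up to 24 h from birth".

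**Echo timing.** The text under Figure 1 says "Echocardiography will be conducted at least twice during the study" and places the two examinations at "1) within 6 h after enrolment in the study and (2) 6–10 h after administration of the last dose of the drug (or placebo". Section 2.4 counts the intervention period from enrolment, with doses every 6 h. A note to Figure 2 also has "up to 6 hours after allocation", but the figure is not shown, so the row it belongs to cannot be confirmed.

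**The concern.** A prevention trial needs to know who was free of the condition when treatment began. Here an infant may enter at up to 24 h of life with PPHN already present, be dosed, and have the first echo some hours later. A positive result then has two explanations: the condition was there at entry, or it arose on treatment. An echo taken after a dose is also not a clean baseline, because it may already reflect the drug.

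Cases already present cannot be prevented. If counted, they add about the same number of events to each arm and shrink the relative difference. The design is sensitive to this because the assumed salbutamol rate is only 0.1%, which leaves almost no room for events that the drug cannot affect.

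**Working it through.** **Inputs.** From section 2.3.2: 4% on placebo, 0.1% on salbutamol, 253 per arm (506 in all), 80% power, α = 0.05. From section 2.3.3: chi-square or Fisher's exact test. Prevalence at entry, π, is not in the document. It is assumed here at 0.5 and 1 percentage point, with a wider range at the end.

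**1. The plan's own figure.** The usual two-proportion formula with pooled variance under the null is

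n = [1.96·√(2p̄(1−p̄)) + 0.8416·√(p₁(1−p₁) + p₂(1−p₂))]² / (p₂−p₁)²

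With p₁ = 0.001, p₂ = 0.04 and p̄ = 0.0205, n is about 206.1, rounded up to 207. The continuity correction, n/4·[1 + √(1 + 4/(n(p₂−p₁)))]², gives 255 per arm. The unpooled version with correction gives 252. The stated 253 is therefore reproduced with a two-sided test and continuity correction, and the sample size is not wrong on its own inputs. Exact two-sided Fisher power at 253 per arm for 4% vs 0.1% is 90%.

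**2. Room for unpreventable events.** Expected events on salbutamol are 253 × 0.001 = 0.25. With π = 0.5% the existing cases alone add 253 × 0.005 = 1.3 per arm, and with π = 1% they add 2.5.

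**3. Existing cases are part of the 4%.** Placebo stays at 4.0%. Salbutamol becomes π + 0.1%. If only new cases are counted, placebo is 4.0% − π and salbutamol 0.1%.

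| π | All cases counted | Fisher power | New cases only | Fisher power | Difference |
|---|---|---|---|---|---|
| 0 | 4.0% vs 0.1% | 90% | – | – | – |
| 0.5 points | 4.0% vs 0.6% | 66% | 3.5% vs 0.1% | 82% | 16 points |
| 1 point | 4.0% vs 1.1% | 44% | 3.0% vs 0.1% | 70% | 26 points |

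Not all of the fall from 90% comes from counting existing cases. Part arises because fewer preventable cases remain. The last column is the part that a new-onset outcome recovers.

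**4. Existing cases come on top of the 4%.** Each arm's rate becomes π + (1−π)p.

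| π | Rates | Fisher power |
|---|---|---|
| 0.25% | 4.24% vs 0.35% | 83% |
| 0.5% | 4.48% vs 0.60% | 76% |
| 1% | 4.96% vs 1.10% | 66% |
| 2% | 5.92% vs 2.10% | 52% |

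Here a new-onset outcome would restore roughly the planned 90%.

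**5. Choice of test.** With the uncorrected chi-square, which section 2.3.3 also allows, exact enumeration gives 96% as planned, 77% for 4.0% vs 0.6%, and 57% for 4.0% vs 1.1%. The level is higher, and the direction and rough size of the loss are the same.

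**The case against.** **The wording points to new onset.** Sections 2.1, 2.3.2, 2.3.3 and 2.6 speak of development or incidence. A reader might infer that the plan counts existing cases as failures of prevention. It does not say so: that would be an inference from silence. What stands is that no stated rule puts the new-onset reading into effect, and that a later analysis plan cannot supply a measurement that was not made before treatment.

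**The first dose is not timed.** A reader might also infer that the first echo always comes after the first dose, so that no pre-treatment record exists. The article does not fix the first dose relative to enrolment. Section 2.5 gives enrolment and allocation separate windows (birth to 24 h, and 6 to 24 h of life), so an echo within 6 h of enrolment may precede allocation in some infants. Hourly FiO2 and saturation add some baseline information, although no echo findings. The supported statement is that the echo may follow the first dose and nothing requires otherwise.

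**Other exclusions help.** Asphyxia, meconium aspiration, diaphragmatic hernia and immediate need for surfactant are excluded, and these are among the causes of PPHN listed in the Introduction. This lowers the likely prevalence at entry but does not make it zero.

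**Article format.** A condensed article may leave out detail. But eligibility, echo timing and the outcome definition are all stated here, and the problem lies in how they combine. Section 2.3.6 does give a rule for infection recognised after entry.

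**Randomisation.** Existing cases should fall equally in both arms. This stands, and it limits the harm to dilution.

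**Conclusion.** The point holds as a design weakness of uncertain size. As written, the plan allows infants with PPHN at entry to be randomised and allows the first echo to follow the first dose. It gives the outcome neither a start time nor a rule for a positive first examination. New and existing cases may then be mixed, and in infants scanned after dosing they cannot be separated. The consequence is a diluted effect and lost power, with no bias towards a false positive.

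The size rests wholly on an assumed prevalence at entry. At 0.5 or 1 percentage point, Fisher power is 66% or 44% if existing cases are part of the 4%, and about 76% or 66% if they come on top of it. In each of these four cases it is below the 80% the trial was sized for. If the prevalence is near zero, the loss is negligible.

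**What to change.** - Reconcile sections 2.3.5, 2.4 and 2.6. The first echo, already planned, and the pre- and post-ductal saturation pair used in the definition should serve as a pre-treatment baseline wherever this does not delay treatment.
- Record the time of both assessments relative to the first dose.
- Define the primary outcome as PPHN first met after randomisation.
- For all infants, including those already enrolled, flag those who met the definition on an assessment made before the first dose. Report the primary analysis with and without them.
- Whether PPHN at baseline should also be an exclusion is for the sponsor to decide. Recruitment was planned from December 2021, so a new exclusion would probably change the population partway through.

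The cost is earlier scheduling of one existing examination and a few infants set apart in the analysis. Infants whose first echo came after dosing stay unclassified, and their number should be reported.

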### Participants timeline

2.5.

T_0_—screening and enrolment (birth to 24 h of life).T_0_—allocation and randomization (6 to 24 h of life).T_1_—first observation period (from randomization to 24 h after randomization).T_2_—second observation period (from 24 to 48 h after randomization).T_3_—extended observation period (from 48 h after randomization to discharge or 7 days of life, depending on which comes first).

### Primary outcome

2.6.

The primary outcome is the percentage of infants who develop PPHN, defined as the need for ventilation with FiO_2_ > 0.30 and features of increased pulmonary pressure on echocardiogram (patent ductus arteriosus or foramen ovale with right-to-left or bidirectional flow, as well as other echocardiographic parameters described below), and/or a > 10% difference between pre-ductal and post-ductal oxygen saturation levels.

### Secondary outcomes

2.7.

The secondary outcomes are the severity of respiratory distress (assessed with the modified TTN Silverman score, presented in Table 1) (32, 33), frequency of need for intubation, duration of NIV, duration of hospitalization, and blood levels of acid–base parameters [pH, partial pressure of CO_2_ (pCO_2_), partial pressure of O_2_, and base excess/deficit] and ions (sodium, potassium, and calcium).

**Table 1 T1:** Modified TTN Silverman score.

	0	1	2
Saturation^a^	>95%	90%–95%	<90%
Intercostal retraction	None	Mild	Continuous
Tachypnea	None	Mild	Continuous
Nasal flaring	None	Mild	Continuous
Expiratory grunting	None	Intermittent	Continuous

TTN, transient tachypnea of the newborn.

^a^
Measurement of post-ductal saturation during oxygen therapy.

### Measures

2.8.

PPHN is defined as the need for ventilation with FiO_2_ > 0.30 and features of increased pulmonary pressure on echocardiogram (patent ductus arteriosus or foramen ovale with right-to-left or bidirectional flow), and/or a > 10% difference between pre-ductal and post-ductal oxygen saturation levels. To evaluate the features of PPHN, echocardiography will be conducted at least twice (Figure 2) using a sector Doppler transducer with a frequency range of 5–12 MHz.

**Figure 2 F2:**
[figure not shown]
The schedule of enrolment, interventions, and assessments in the REFSAL study. D – possible performance of an additional examination according to the decision of the attending physician. Obligatory in the case of intubation, pneumothorax, or sudden deterioration of the patient's condition – procedures should be performed within 6–10 h of the patient's deterioration. ^a^Blood count, Ionogram made of venous blood, Blood gases. ^b^Every 1 h within 6 hours of randomization, every 2 h between 6 and 24 h, and every 6 h between 24 and 48 h after randomization and 1 and 4 h after the end of each dose/placebo and at the time when intubation is necessary. ^c^Every 1 h within 6 h of randomization, every 2 hours between 6 and 24 h, every 6 h between 24 and 48 h after randomization, and 1 and 4 h after the end of each dose/placebo and at the time of necessity for intubation. * Adverse events monitored from enrolment until the end of the extended follow-up period, that is, up to seven days of age or hospital discharge. **up to 6 hours after allocation. ^+^6–10 hours after the last dose of IMP.

The examination will include the following:
a.Estimation of systolic pulmonary arterial pressure (SPAP) accounting for tricuspid valve regurgitation (using the modified Bernoulli equation) and right atrial pressure (RAP): SPAP will be estimated according to the following formula: SPAP (mmHg) = 4 × (VmaxTR)2 + RAP, where VmaxTR is the peak velocity of tricuspid regurgitation (in minutes/seconds). RAP is generally assumed to be approximately 3–5 mmHg (34).b.Evaluation of direction and time (in minutes) of blood flow through the ductus arteriosus (right-to-left and left-to-right): This will be obtained from a parasternal short-axis view.c.Determination of pulmonary artery flow, including measurements of right-sided systolic time intervals at the pulmonary valve in the parasternal short-axis view: This will include time to peak pulmonary artery flow velocity (TPV), right ventricular ejection time (RVET), and TPV/RVET ratio.d.Assessment of the tricuspid annular plane systolic excursion (TAPSE): The examination will be conducted in an apical four-chamber projection using M-mode. Gating will be set near the attachment of the tricuspid valve to the myocardium.e.Determination of the myocardial performance index (MPI, also known as the Tei index) for the right ventricle: The examination will be conducted in an apical four-chamber projection (to monitor the diastolic flow through the tricuspid valve using a pulse-wave Doppler) and in a parasternal short-axis view (to monitor the pulmonary artery flow). The isovolumetric contraction time (ICT), isovolumetric relaxation time (IRT), and ejection time (ET) will be measured, and MPI will be calculated using the formula (ICT + IRT)/ET (35, 36). The MPI will also be measured using tissue Doppler echocardiography.f.Calculation of the eccentricity index (EI), defined as the ratio of the left ventricle dimensions (D1/D2 ratio) measured along the short axis of the heart: The examination will be conducted in a parasternal short-axis view at the level of the mitral valve.g.Assessment of the right ventricular systolic duration to diastolic duration ratio (S/D ratio): Systolic duration is the duration from the onset to the termination of tricuspid valve regurgitation, and diastolic duration is the time between the two jets of tricuspid regurgitation. The right ventricular S/D ratio is calculated from the Doppler signal of the tricuspid valve regurgitation (34).h.Assessment of the size of foramen ovale.

#### Echocardiographic criteria for diagnosis of PPHN

2.8.1.

1.Pulmonary arterial pressure >33% of the systemic arterial pressure.2.Presence of right-to-left flow (that lasts >30% of the cardiac cycle) through the ductus arteriosus and/or foramen ovale.3.TPV/RVET ratio <0.3 for mild PPHN and <0.23 for severe PPHN.4.TAPSE <1 cm.5.Right ventricular MPI >0.25.6.D1/D2 ratio >0.81.

#### Evaluation of TTN

2.8.2.

The modified TTN Silverman score (32, 33) (Table 1) will be used to assess the severity of the respiratory disorder. The sum of the points will correspond to the Silverman score (0–10 range; the higher the score, the more severe the respiratory distress).

Based on Szymanski et al.'s study (13) on the evaluation of TTN, we propose to use a modified LUS score in neonates with respiratory distress, which includes posterior instead of lateral lung fields, and a five-grade rating scale, where “0” corresponded to normal lung and “4” indicated the presence of pulmonary consolidations (13). The sum of all four area scores will be the total LUS score, which will range from 0 to 16.

For NIV, the following information will be collected: start time, total duration in days, initial/maximal pressure, and initial/maximal FiO_2_.

### Early termination

2.9.

A patient can be withdrawn from the study at any stage following the decision of the principal investigator or withdrawal of consent from the parent/legal guardian. Early termination can also occur in the following cases:
•An adverse event (AE) likely related to the treatment intervention.•The need for surfactant administration.The need for intubation or rapid worsening of respiratory function, which is defined as follows:
a.An increase in oxygen demand by >50% for >30 min or an increase in pCO_2_ above 70 mmHg in two consecutive examinations of blood acid–base parameters performed at a 1-h interval.b.Repeated (more than twice in 1 h) incidents of apnea lasting >20 s, defined as cessation of breathing and bradycardia <100 beats per minute with oxygen saturation <80%.c.The need for manual ventilation using a bag valve mask.•Improvement of respiratory function, allowing NIV discontinuation.•Severe violation of the eligibility criteria or study protocol.Early termination of participation in the study will result in the discontinuation of the treatment with salbutamol. After treatment discontinuation, the patient will be followed up according to the study protocol until the seventh day of life or hospital discharge.

In every case, the reason for withdrawal will be described in the electronic case report form. Patient data collected before the withdrawal can be included in the analysis by the sponsor.

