#### Sample size

2.3.2.

A sample size of 506 patients (253 in each group) was estimated to provide 80% power at *α *= 0.05 to detect a difference in the incidence of PPHN between groups, assuming an incidence of 0.1% in the salbutamol group vs. 4% in the placebo group. Assuming a 20% dropout rate (due to the decision of the principal investigator, withdrawal of consent from a parent/legal guardian, or other reasons described in the subsection “Early termination”), the sample size was fixed at 608 patients.

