#### Early-onset infection/pneumonia procedure

2.3.6.

Diagnostics of early-onset infection/pneumonia follows the protocol in force. As the diagnosis of early-onset infection/pneumonia can be made later than in the first 6 h of the infant's life, patients with an infection (diagnosed on the basis a positive blood culture) or pneumonia (diagnosed on the basis of a chest x-ray) included in the study will be analysed as a separate subgroup.

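### The sample-size section counts early-termination events as dropout, and section 2.9 makes only pre-withdrawal data optionally usable; read literally, PPHN diagnosed after early termination can be left out of the primary comparison

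*Protocol article*

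**What the plan says.** Four places in the protocol article bear on which infants count in the primary comparison.

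- **Section 2.3.2, Sample size.** The target is 506 infants, 253 per group, "assuming an incidence of 0.1% in the salbutamol group vs. 4% in the placebo group". It is raised to 608 for 20% dropout. Dropout is described as investigator decision, withdrawal of consent, "or other reasons described in the subsection" on early termination.
- **Section 2.9, Early termination.** The reasons include a likely treatment-related adverse event, need for surfactant, need for intubation or rapid worsening, improvement that lets NIV stop, and severe violations. After treatment stops, "the patient will be followed up according to the study protocol until the seventh day of life or hospital discharge". The section ends: "Patient data collected before the withdrawal can be included in the analysis by the sponsor".
- **Figure 2 note.** Additional examinations are "Obligatory in the case of intubation, pneumothorax, or sudden deterioration of the" patient's condition, and are to be done within 6–10 h of the deterioration.
- **Section 2.3.6.** Infants with infection or pneumonia, which may be diagnosed after the first 6 h of life, "included in the study will be analysed as a separate subgroup".

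Section 2.6 defines PPHN through ventilation with FiO2 above 0.30 plus echocardiographic signs, and/or a difference of more than 10% between pre- and post-ductal saturation.

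**The concern.** Dropout should mean that the outcome is not known. Here it includes events that are part of the outcome process. Need for intubation is a secondary outcome and is named in the hypothesis. Rapid worsening includes a rise in oxygen demand of more than 50%. From the lowest starting FiO2 of 0.21, a relative rise of that size gives more than 0.21 × 1.5 = 0.315, which already passes the FiO2 threshold in the PPHN definition. Infants who end participation for worsening are therefore among the likeliest to have PPHN.

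The closing sentence of section 2.9 then covers only data collected before withdrawal and leaves even their use to the sponsor. If withdrawal there includes early termination, the examination that would establish PPHN after a deterioration falls on the wrong side of the line. Whether an infant counts would then depend on its outcome and on a choice made by the sponsor. With so few expected events, a handful of such decisions could settle the result.

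The infection and pneumonia sentence raises a smaller question of the same kind. The Introduction lists sepsis and congenital pneumonia as causes of PPHN, so this group may hold primary events, and the text does not say whether it stays in the main comparison.

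**Working it through.** **Inputs.** From section 2.3.2: PPHN rates of 0.1% and 4%, 80% power, α = 0.05, 253 per group, 20% dropout, 608 in total. From section 2.3.1: 1:1 allocation. From section 2.3.3: chi-square or Fisher's exact test. Two-sided testing is assumed, as sidedness is not stated. The share of PPHN cases lost is assumed throughout.

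**Step 1: the plan's own figure.** For two proportions with pooled variance under the null, p̄ = (0.001 + 0.04)/2 = 0.0205 and

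n = [1.96·√(2·0.0205·0.9795) + 0.8416·√(0.001·0.999 + 0.04·0.96)]² / 0.039² = 206.05, so 207 per arm.

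With the continuity correction, n/4 · [1 + √(1 + 4/(n·0.039))]² = 254.8, so 255 per arm or 510 in total. This is within 1% of the stated 506, which is therefore reproduced.

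**Step 2: the inflation.** 506 × 1.2 = 607.2, giving 608, or 304 per arm. A true 20% loss leaves 608 × 0.8 = 486, or 243 per arm. (Dividing instead gives 506/0.8 = 632.5, so 633. That is a side matter.)

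**Step 3: expected cases if all are analysed.** Placebo: 304 × 0.04 = 12.2. Salbutamol: 304 × 0.001 = 0.3. Exact Fisher power, summed over both binomial distributions, is 96%.

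**Step 4: loss of cases.** Suppose 243 per arm are analysed and a share g of all PPHN cases is lost in both arms. The analysed rates are then 304 × 0.04 × (1 − g)/243.2 and 304 × 0.001 × (1 − g)/243.2. At g = 20%, cases are lost at the same rate as everyone else, so the loss is unrelated to outcome.

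| Share of PPHN cases lost (assumed) | Placebo cases left | Analysed rates | Exact Fisher power |
|---|---|---|---|
| 20% | 9.7 | 4.0% vs 0.10% | 88% |
| 30% | 8.5 | 3.5% vs 0.09% | 80% |
| 50% | 6.1 | 2.5% vs 0.06% | 52% |
| 60% | 4.9 | 2.0% vs 0.05% | 33% |

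Power falls steeply because, with equal arms and no salbutamol case, the two-sided Fisher p-value for k placebo cases is close to 2 × 0.5^k: about 0.063 for five and 0.031 for six. At least six placebo cases must therefore remain.

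**Step 5: the passages side by side.**

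| Place | What it implies for an infant who is intubated |
|---|---|
| 2.3.2 | Part of the 20% not expected to be evaluable |
| 2.9, follow-up sentence | Observed to day 7 or discharge |
| Figure 2 note | Examined within 6–10 h after the event |
| 2.9, closing sentence | Data before withdrawal may be used; later data not mentioned |

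The second and third rows collect the outcome. The first and fourth give grounds for not using it.

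**The case against.** The strongest reply is that no exclusion rule exists. Section 2.9 ties early termination to stopping salbutamol and keeps the infant under observation, and the Figure 2 note shows that the plan means to capture PPHN after deterioration. The closing sentence may concern only infants withdrawn by the investigator or by parents, the cases with which the section opens. Section 2.3.2 is an allowance for sizing and does not define an analysis set. Section 2.3.3 compares the two groups without naming exclusions. The efficacy set may well be in a statistical analysis plan that is not shown, so its absence here is no defect.

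Much of this stands. A reader might infer that the protocol removes these infants from the primary analysis; it does not say so. Four further inferences also go beyond the text:

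- The separate subgroup for infection or pneumonia may be an added analysis and need not mean removal.
- Infants who improve enough to stop NIV are unlikely PPHN cases, so losing them costs numbers more than events.
- The abstract's denominator of infants with TTN, against infants in section 2.6, is abstract shorthand and not a second population.
- A raised false-positive rate needs arm-specific loss. If salbutamol had no effect (4% in both arms), 243 per arm were analysed, and half of salbutamol cases but 20% of placebo cases were lost, Fisher's test would reject in about 10% of trials, against 2.9% with 20% lost in both. No passage supports such a difference: doctors and nurses are blinded, and follow-up continues after stops for adverse events.

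What the reply does not remove is the conflict in step 5. Section 2.9 speaks of recording the reason for withdrawal in every case after listing all the early-termination reasons, so its wording does not confine the closing sentence to withdrawal of consent. An analysis plan that takes all randomised infants would contradict the dropout definition and the optional wording here.

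**Conclusion.** The point holds as an unreconciled contradiction that permits outcome-dependent loss of PPHN cases. It is not shown that such loss is planned or will occur. The stated text, followed literally, lets PPHN diagnosed after early termination be left out and gives the sponsor a choice over the earlier data.

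The possible cost in power depends on assumed losses. Against 96% with everyone analysed, 243 per arm with 30% of all cases lost in both arms still gives the planned 80%; 50% gives 52% and 60% gives 33%. These figures rest on the plan's rates of 4% and 0.1%, a two-sided test, and equal proportional loss in both arms. The wording should be settled before unblinding, since about 12 expected placebo cases leave little room for discretion.

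**What to change.** 1. In section 2.9, separate stopping study treatment from withdrawal of consent, and use one term for each.
2. State that the primary analysis includes all randomised infants by allocated arm and counts PPHN up to day 7 or discharge, whether or not treatment was stopped.
3. In the closing sentence of section 2.9, replace *can* with *will*, and cover data from before and after treatment stop unless consent to data use is withdrawn.
4. In section 2.3.2, limit the dropout allowance to true loss of the primary outcome.
5. In section 2.3.6, state that infants with later-diagnosed infection or pneumonia stay in the primary comparison, with the subgroup as a supportive analysis.

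The changes are to wording only: follow-up to day 7 or discharge and the examinations after deterioration are already planned. The price is that the estimate will include infants who received little study drug, so it describes the effect of assignment to salbutamol and not of a full course.
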